### Sample size determination

In line with the proof-of-concept study design, a small sample of up to ten cases is sufficient to evaluate if the intervention works as described in theory [14]. This approach allows for the exploration of potential side effects and the subjective experiences of the participants. Every single case within the intervention group holds significant clinical relevance and is of interest.

The first AAS case control study from our research group [27,28] found significant effects between the groups for measures of psychopathology with effect sizes ex =0.27. With a power of 80 % and a wish to detect effects of moderate level (Cohen's *d* = 0.4), a total sample of 52 participants is needed.

In the current study, the recruitment target for both the intervention group and comparison group is 25–30.

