### Data analysis plan

Data analyses will follow a full analysis set, with a per protocol plan. Descriptive statistics will be used when appropriate and for reported adverse events. For between-group comparisons and to control for the effect of baseline characteristics, we plan to use General Linear Mixed Models (GLMM) with a within subject repeated measures design at baseline, 6 months and 12 months. In cases where the outcomes do not meet the normality assumption, we will apply a General Alinear Mixed Models (GAMM) approach. The results of statistical analyses will be performed using 95 % CIs, and a two-sided P value of < 0.05 will be used to indicate statistical significance. General linear models may be utilized in cases where GLMM/GAMM is considered inappropriate. Two sample *t*-tests will be used for between-group comparisons of numerical variables, when we see no need to adjust for confounding variables. Numerical data not following normal distribution will be presented as medians (25th-75th percentiles), using non-parametric tests such as the Wilcoxon rank sum tests (Mann-Whitney) to compare differences between groups. Chi^2^-tests and Fischer's exact will be applied for categorical variables. Per protocol analysis will be applied in cases of missing data to detect any discrepancy that might affect the robustness of the results. All statistical calculations and analyses will be conducted using up-to-date versions of the statistical software STATA and SPSS.

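### The stated total of 52 participants does not follow from 80% power at Cohen's d = 0.4; in a two-group comparison it corresponds to d of about 0.8

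*Protocol article*

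**What the plan says.** The Sample size determination section of the protocol article first refers to between-group effects on psychopathology in an earlier case-control study by the same group. It then asks for 80% power to detect "effects of moderate level (Cohen's *d* = 0.4") and concludes that "a total sample of 52 participants is needed". It adds that "the recruitment target for both the intervention group and comparison group is 25–30". The section names no test, no within-subject correlation and no number of repeated measures.

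The Data analysis plan supplies the rest: "a two-sided P value of < 0.05 will be used to indicate statistical significance". Between-group comparisons use two-sample t-tests where no adjustment is thought necessary. Otherwise they use mixed models with repeated measures at baseline, 6 months and 12 months.

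The section on self-reported mental health, well-being and withdrawal symptoms has both groups complete the questionnaires every second week for 16 weeks. Only the intervention group completes them at 6 and 12 months.

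**The concern.** The total of 52 is far below what the stated effect size, power and significance level require for two independent groups.

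The comparison is a central one. The Aims make a greater reduction of withdrawal symptoms than with no intervention part of the primary aim, and symptom change is the first primary outcome. A reader who relies on the sentence could take a non-significant result as evidence against a moderate effect, when a simple comparison of this size would usually miss one. The article also says that the results may inform the sample size of later trials, so an unclear effect-size scale could be carried forward.

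**Working it through.** **Inputs.** Power 80%, d = 0.4, total 52 (26 per group at 1:1) and 25–30 per group come from Sample size determination. Two-sided 5% and the two-sample t-test come from the Data analysis plan.

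**Step 1: the plan's figure from its own inputs.** For two equal independent groups, the normal approximation is n per group = 2(z₀.₉₇₅ + z₀.₈₀)² / d².

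- d = 0.4: 2(1.960 + 0.842)² / 0.16 = 98.1, so 99 per group (198 in total). The noncentral t gives 99.1, so 100 per group (200 in total).
- The figure of 52 is not reproduced. Using the normal approximation, a one-sided test still needs 78 per group (156 in total). Unequal allocation raises the total to 222 (2:1) or 264 (3:1).

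**Step 2: what 52 does correspond to.**

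- Two groups, d = 0.8: 2(2.802)² / 0.64 = 24.5, so 25 per group. The noncentral t gives 25.5, so 26 per group, which is 52 in total. Power at 26 per group is about 81%.
- Two-group analysis of variance, Cohen's f = 0.4: 51.05, so 52 in total. For two equal groups f = d/2, so this is again d = 0.8.
- Group-by-time interaction, f = 0.2, two time points, correlation 0.5: 52 in total. The effect is then a difference in change of 0.8 SD.
- Paired test, standardised mean change 0.4: 51.0, so 52 men measured twice in one group. The intervention group is to have 25–30.

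**Step 3: what the design gives in an unadjusted comparison at one time point** (noncentral t, two-sided 5%).

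| n per group | Power at d = 0.4 | d detectable with 80% power |
|---|---|---|
| 25 | 28.3% | 0.81 |
| 26 | 29.3% | 0.79 |
| 30 | 33.2% | 0.74 |

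**Step 4: how far repeated measures could help.** Assume a common correlation ρ between all scores (compound symmetry), m post-baseline scores averaged, and adjustment for baseline. The residual variance is multiplied by v = (1 + (m − 1)ρ)/m − ρ², so the effective effect is 0.4/√v. With 26 per group:

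| m | ρ | v | 0.4/√v | Power |
|---|---|---|---|---|
| 1 | 0.5 | 0.750 | 0.46 | 37% |
| 1 | 0.7 | 0.510 | 0.56 | 51% |
| 2 | 0.5 | 0.500 | 0.57 | 52% |
| 2 | 0.7 | 0.360 | 0.67 | 65% |
| 8 | 0.5 | 0.3125 | 0.72 | 72% |
| 8 | 0.7 | 0.2475 | 0.80 | 81% |

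With a single post-baseline score, 80% is reached only at ρ of about 0.87. The values of ρ are assumptions; the article gives none. The m = 2 rows mirror the 6- and 12-month schedule in the Data analysis plan, but the comparison group has no questionnaires at those times. The m = 8 rows mirror the fortnightly schedule, which both groups do follow but which the described model does not use.

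**The case against.** The strongest objection is that the main between-group analysis is a mixed model, with t-tests kept for cases where no adjustment is needed. A figure near 29% therefore does not describe the study's power as a whole. That stands. A model using all eight fortnightly scores could reach about 80% at d = 0.4 with 52 men if the correlation were near 0.7. This does not rescue the sentence, because the section claims no such gain and the model as described uses time points at which only one group is measured.

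A second objection is that this is a small pilot, its size is listed as a limitation, and a pilot needs no power calculation. That is fair, and it is why no change of design follows. But the section does make a power claim, and the claim does not follow from its inputs.

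A reader might infer more than the article supports:

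- **That the section contradicts itself by saying that "a small sample of up to ten cases is sufficient to evaluate if the intervention works as described in theory".** That sentence concerns proof of concept, side effects and participants' experience. The 52 belongs to the between-group comparison. Two purposes may have two numbers.
- **That the target falls short because 25 + 25 = 50.** The range includes 26 + 26 = 52, and the gap moves power at d = 0.4 only from 29% to 28%.
- **That a dropout allowance is missing.** An article commonly leaves this to the full protocol.
- **That an f of 0.4 was entered as a d of 0.4.** The arithmetic fits, but nothing in the text shows it, so it remains conjecture. The earlier effect of 0.27 is given on no identifiable scale and settles nothing.

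**Conclusion.** The sample size sentence is wrong as written. For two independent groups at two-sided 5%, 80% power at d = 0.4 needs about 200 participants, nearly four times the stated 52, and 52 corresponds to d of about 0.8. This rests only on figures in the article and on reading the total as covering the two groups, which the adjacent target for each group supports.

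The power of 28–33% at d = 0.4 is conditional on an unadjusted comparison at one time point. Under the assumptions in the working, baseline-adjusted models with 26 per group give about 37–81%, depending on the correlation and the number of scores. It would go too far to say that the trial has 29% power under any analysis, or that it must recruit 200 men. The claim should be corrected because it bears on a primary aim, but the design can stay as it is.

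**What to change.** Replace the sentence with one that the target supports, for example: *With 25–30 per group, an unadjusted two-sided 5% comparison at a single time point has 80% power for d of about 0.74–0.81, and about 30% power for d = 0.4.*

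Two alternatives would also serve:

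- State the power of a specified baseline-adjusted mixed model on the fortnightly scores, with its assumed correlation and number of measures. The time points in the Data analysis plan would then have to match.
- Drop the power claim and present the study as a pilot.

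Each is a change of wording, with no extra recruitment, visits or data. The cost is that the first option states a less favourable figure.

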### Scientific rationale for study design

The chosen design served three primary purposes (a) to assess the feasibility and acceptability of the intervention, (b) to evaluate its safety, and (c) to examine its effect on symptoms and objective measures of hypogonadism. The cohort design for the intervention group allowed for investigating potential health risks reduction following cessation of AAS use. Although a randomized controlled trial (RCT) is considered the gold standard methodology, conducting a preliminary test of the intervention before proceeding to an RCT is essential. Additionally, this approach facilitates the determination of effect sizes for use in sample size calculations for future RCTs [29]. However, it is acknowledged that the comparison group may differ from the intervention group on certain variables, as they may not share the same intention to permanently cease AAS use.

The study exclusively recruits male participants as we investigate the effect of treatment of androgen deficiency due to AAS induced male hypogonadism. The primary endpoints (symptoms of hypogonadism such as depression, anxiety, fatigue, reduced libido, and erectile dysfunction, and other symptoms related to AAS use) were developed in collaboration with a user panel comprising people with prior AAS experience and clinicians from the outpatient SUD clinic with experience of providing treatment to the patient group. These endpoints are considered reliable clinical indicators of the intended intervention effect.

### User participants’ input into design

The research questions and design for the proposed study have been discussed and developed in collaboration with a user panel of five men with former AAS use. The research questions, design, inclusion criteria and variables (background information, health risk examinations and self-report questionnaire) for the proposed study was discussed and developed in workshops with the user panel, clinicians, and researchers. The panel strongly approved testing the proposed off-label intervention as well as health risk examinations before, during and after the intervention. The user panel were also clear that if randomized control design was chosen, it would lead to drop out in the control group. Members of the panel took part in testing of the self-report questionnaire and development of ads for social media. They also suggested recruitment strategies in certain gyms, social media and through information to general practitioners and SUD treatment facilities.

### Ethics approval and consent to participate

The CloTASH off-label pilot intervention study is approved by the Norwegian Regional Committee for Medical Research Ethics (33872), the Norwegian Medicines Agency (21/18081–9) with EudraCT-number 2020–005938–15 and the Data Protection Officer at Oslo University Hospital (20/27593). All participants will receive oral and written information about the study and written formal consent will be collected.

The ongoing study for the comparison group: “Cycling with anabolic steroids: studying how large fluctuations in sex hormones affect brain chemistry, functional network, cognition and emotions” is approved by Norwegian Regional Committee for Medical Research Ethics (2013/601) and the Data Protection Officer at Oslo University Hospital (18/10139–3). Written consents are collected from all participants prior to inclusion. Participants are compensated with NOK 500 (≈$50) for taking part in the study and have the opportunity to discontinue the study at any point.

The research will be carried out according to the Helsinki declaration*.* Emphasis is placed on voluntary participation and that refraining from participation is possible at any stage in the study period prior to data publication without affecting the access to SUD outpatient treatment. All participants in the intervention are insured against adverse events attributable to study drug occurring during or after participation, through Project leader´s membership in the Norwegian Drug Liability Association. The participants in the intervention group are not compensated for taking part in the study, but study medication and physical health examinations in the study will not involve any costs. The participants will pay deductibles as patients in outpatient substance use disorder treatment and at potential follow-ups through somatic health services where indicated. All pathological findings of clinical relevance will be evaluated by physicians connected to the study and investigated further on indication.

## List of abbreviations

**Table utbl0002:** 

AAS	Anabolic androgenic steroids
SUD	Substance Use Disorder
HPG	Hypothalamic-Pituitary-Gonadal
ASIH	Anabolic-androgenic Steroid Induced Hypogonadism
PCT	Post Cycle Therapy
PIEDs	Performance and Image Enhancing Drugs
CC	clomiphene citrate
SERM	Selective Estrogen Receptor Modulator
GnRH	Gonadotropin-Releasing Hormone
LH	Luteinizing Hormone
FSH	Follicle Stimulating Hormone
TRT	Testosterone Replacement Therapy
ALT	Alanine transaminase
AST	Aspartate transaminase
OUH	Oslo University Hospital
hCG	human Chorionic Gonadotropin
T	Testosterone
BMI	Body Mass Index
ECG	Electrocardiogram
BP	Blood Pressure
HR	Heart Rate
CAR	Carotid Artery Reactivity
DXA	Dual energy X-ray absorptiometry
TLM	Total Lean Mass
TFM	Total Fat Mass
VAT	Visceral Adipose Tissue
GLMM	General Linear Mixed Models
GAMM	General Alinear Mixed Models
RCT	Randomized Control Trial
CTCAE	Common Terminology Criteria for Adverse Events
SAE	Severe Adverse Events
SUSAR	Suspected Unexpected Severe Adverse Reaction

## Protocol validation

Not applicable

## Limitations

This non-randomized proof-of-concept intervention study with a small number of participants, is the first study to test off-label use of CC with the intention to restart endogenous testosterone production upon cessation of AAS use among men with AAS induced hypogonadism. The study will compare symptoms of AAS induced hypogonadism and other AAS-related side effects between the group receiving CC and a group of male AAS users not receiving the intervention. The comparison group differs from the intervention group as the participants may have less serious AAS use and less symptom burden during use as they mostly use AAS as cycles with an intention to cease use only temporarily. Moreover, the 12 months follow-up on examination of health risks in the intervention group may be too short as sperm quality is found to take up to 3 years to recover [15] and men with former AAS use is found to have lower plasma testosterone levels and more symptoms suggestive of hypogonadism than healthy controls several years after AAS cessation [30]. Finally, many health risks are associated with AAS use [[4], [5], [6]], and measures of a selection of health risks are included in this study. However, detailed, and frequent monitoring using objective biological measures is a strength and the study may provide valuable clinical insights, enabling the exploration of whether adjustments are needed for the intervention. Furthermore, the results may be used to determine the sample size and informing the design of future RCT or case comparison studies.

## Supplementary material *and/or* additional information [OPTIONAL]

None.

## Data Availability

No data was used for the research described in the article. No data was used for the research described in the article.
